#### Eligibility criteria

Patients need to fulfill the following criteria to be included in the study: 1) adult (>18 years); 2) histologically confirmed WHO grade I (pilocytic astrocytoma, pleomorphic xanthoastrocytoma, subependymal giant cell astrocytoma or subependymoma), WHO grade II (astrocytoma, mixed oligo-astrocytoma, oligodendroglioma or ependymoma), or WHO grade III glioma (anaplastic astrocytoma, anaplastic oligodendroglioma, anaplastic oligo-astrocytoma or anaplastic ependymoma); 3) history of epilepsy, defined as the history of at least one seizure except for acute symptomatic seizures, and treatment with AEDs; 4) having undergone anti-tumour treatment (surgical resection, brain irradiation and/or chemotherapy); 5) stable disease with absence of clinical or radiological signs of tumour recurrence, at least during the past 12 months; 6) seizure freedom for at least 12 months from the date of last surgery, irradiation or chemotherapy cycle, *or* seizure freedom for at least 24 months from the last seizure after the last anti-tumour treatment.

### Intervention

The patient and the treating physician make a shared decision on the preferred treatment (continuation or withdrawal of AED). In case of deciding against the withdrawal of AEDs, patient’s and/or physician’s reasons for continuing are explicitly recorded. In case of deciding to withdraw, AEDs are tapered according to a fixed schedule: a step-wise 50% dose reduction takes place every 2 weeks. The minimally required reduction of total daily dose is as follows: valproic acid: 250 mg; levetiracetam: 250 mg; carbamazepine: 100 mg; oxcarbazepine: 150 mg; phenytoin: 50 mg; clobazam: 2.5 mg; lamotrigine: 25 mg; topiramate: 25 mg; clonazepam: 0.25 mg; and lacosamide: 50 mg. When the patient uses 2 or more AEDs, the last add-on AED will be withdrawn first and the primary AED (typically valproic acid, levetiracetam or carbamazepine) will be withdrawn thereafter.

Two groups of patients will be analysed, depending on the outcome of the decision-making process: one group consists of patients whose AEDs will be withdrawn, and the other group consists of patients whose AEDs will be continued. Standard follow-up in both groups takes place after 3, 6, 12, 18 and 24 months. During follow-up, data about AED treatment, including details on the withdrawal where applicable, as well as data about seizure frequency and type, adverse effects, and clinical and radiological brain tumour progression will be collected. The study follow-up will be part of the regular follow-up for those patients at the neuro-oncology outpatients’ clinic. In case of seizure recurrence, AEDs will be adapted or restarted according to the expertise of the treating physician.

### Measurements

#### Baseline characteristics

After the patient has provided informed consent, we will collect information on demographics, seizure onset, seizure type and frequency, date of the last seizure, AED type and dose, adverse effects, as well as data on past anti-tumour treatments, tumour characteristics including histological subtype and location, and neurological and radiological findings.

#### Primary outcome measures

The two primary outcome measures are: 1) the outcome of the shared-decision making on AED withdrawal or continuation, and decision related arguments, and 2) seizure freedom at 12 months and 24 months of follow-up.

#### Secondary outcome measures

Secondary outcome measures are seizure type and frequency in case of seizure recurrence, additional neurological symptoms, adverse effects related to AED treatment or AED withdrawal, other anti-tumour treatments and tumour progression. In case of tumour progression, the time to clinical or radiological progression will be evaluated as well. According to the response assessment in neuro-oncology (RANO) criteria, clinical progression is defined as a definite clinical deterioration that is not attributable to other causes apart from the tumour or a decrease in corticosteroid dose. Radiological progression is defined as a ≥25% increase in the area of the lesions on T2 or FLAIR MRI, or the development of new lesions or increased or new areas of enhancement [23],[39].

At the last follow-up, patient’s decision to withdraw or continue AEDs will be evaluated, using a study-specific questionnaire on patient’s satisfaction with the decision.

### Sample size

Based on the current population of patients with WHO grade I-III glioma with epilepsy receiving treatment in one of the three referral centers, we estimate that in one year a total of 100 patients will be eligible for this study. The number of patients who will actually withdraw their AEDs, will depend on the outcome of the shared decision-making process. Currently, there are no data on patients’ willingness to withdraw AEDs in this specific population. A retrospective study showed that in 42% of patients with intra-axial brain tumours AEDs were withdrawn after surgery as part of routine clinical practice, although patients on prophylactic AED treatment were also included in this analysis [38]. A cautious estimate is that at least 30 percent of the patients will be willing to withdraw AEDs. As this is an observational study that is not primarily aimed at exploring differences between the 2 groups, no formal sample size calculation can be made. A total number of 100 patients, with at least 30 patients in each group, should be sufficient to complete a prediction model, using 3 co-variates. We expect that less than 5% of the eligible patients are unwilling to participate, as this study is mostly part of routine clinical practice and because of the non-interventional character.

### Statistical analyses

#### Descriptive statistics

Baseline patient characteristics and information about seizure freedom and seizure recurrence, AED treatment and withdrawal, tumour symptoms, tumour recurrence and additional anti-tumour treatments will be outlined by means of descriptive statistics.

#### Univariate analysis

With logistic regression analysis, univariate variables (such as age, gender, treatment, seizure type etc.) showing an association (p < 0.10) with the decision to withdraw AEDs will be identified, as well as univariate variables showing an association (p < 0.10) with seizure recurrence.

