## Methods/Design

### Design and overview

This is a prospective, observational study exploring the decision-making process on the withdrawal or continuation of AEDs in low-grade and anaplastic glioma patients with stable disease and prolonged seizure freedom after anti-tumour treatment, and the effects of AED withdrawal or continuation on seizure freedom. Over a one-year period, we aim to include 100 glioma patients, who will be followed for a duration of at least 24 months. We primarily aim to improve current knowledge on the patient’s and physician’s willingness to withdraw AEDs in brain tumour patients, and to identify the rate of successful AED withdrawals, i.e. that AED’s are withdrawn completely without seizure recurrence. We hypothesize that 1) approximately half of the participants will be willing to withdraw AEDs, and 2) that there will be no significant difference in seizure freedom at last follow-up between patients who have withdrawn and those who have continued their medication.

The study is approved by the institutional review board of the VU University Medical Center (registration number 2013/288).

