#### Multivariable analysis

Next, a multivariable logistic regression analysis will be performed to identify independent predictors of the decision to withdraw AEDs. All variables that are univariately associated with this outcome measure will be entered as possible predictors in a multivariable logistic regression analysis. With a backward selection procedure, using a p-value of 0.10 as the removal criterion, significant independent predictors will be identified. Moreover, we will determine predictors of seizure recurrence. A similar analysis will be performed with seizure recurrence as dependent outcome variable. Variables (such as tumour location, pre-operative seizure frequency, response on MRI, etc.) will be entered as possible predictors in both multivariable logistic regression analyses, using the aforementioned criteria. Note that this analysis can only be performed in case of enough statistical power.

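### Two rounds of p-value selection at 0.10 over an open candidate list, with no limit matching the 3 covariates in the sample-size section, will often yield false independent predictors

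*Protocol article*

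**What the plan says.** The rule is spread over three sections of the protocol article.

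- **Univariate analysis.** For the first outcome, variables "showing an association (p < 0.10) with the decision to withdraw AEDs will be identified". The second outcome, recurrence, gets an identical screen at the same threshold. Four variables are named as examples (age, gender, treatment, seizure type) and the list is left open.
- **Multivariable analysis.** "All variables that are univariately associated with this outcome measure will be entered as possible predictors". Backward selection follows: "using a p-value of 0.10 as the removal criterion, significant independent predictors will be identified". The same is planned for seizure recurrence. Three more examples are given for both models (tumour location, pre-operative seizure frequency, response on MRI), again open-ended. The section ends by making the analysis conditional on sufficient power, without a figure.
- **Sample size.** The planned 100 patients, of whom no fewer than 30 are expected in either group, "should be sufficient to complete a prediction model, using 3 co-variates".

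Neither analysis section carries the limit of 3 forward, either to the candidates or to the final model.

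**The concern.** The data a model needs depend on how many candidates are tried, not only on how many survive. The sample-size section argues for 3 covariates. The analysis sections name more than twice that number and let every variable that passes the screen enter.

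Both steps use p-values from the same patients at a lenient threshold, and whatever remains is labelled significant and independent. A two-sided p below 0.10 means an estimate at least 1.645 standard errors from zero. So every noise variable that passes the screen has, by construction, a univariable 90% confidence interval that excludes an odds ratio of 1. Ordinary p-values and intervals after this selection ignore how the variables were chosen.

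At stake is whether the study names false drivers of the withdrawal decision or false risk factors for recurrence. The Discussion says that risk factors for recurrence will be studied and that the results of the study may eventually inform recommendations.

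**Working it through.** **1. The plan's own figure.** The cautious estimate is that 30% of patients withdraw ("A cautious estimate is that at least 30 percent of the patients will be willing to withdraw AEDs"). With 100 patients, the smaller class in the decision model is 0.30 × 100 = 30, and 30 / 3 = 10 patients in that class per covariate. The figure of 3 is therefore consistent with a rule of ten per covariate. The article names no rule, so this is an inference.

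**2. The same ratio for the candidates named.** Four plus three examples make seven. 30 / 7 = 4.3 per candidate. Under the hypothesis that "approximately half of the participants will be willing to withdraw AEDs", 50 / 7 = 7.1. No number of recurrences is given, so no ratio can be derived for the recurrence model.

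**3. False selection by formula.** With k independent noise candidates, each tested once at 0.10, the chance that at least one passes is 1 − 0.9^k. For two models treated as independent it is 1 − 0.9^(2k).

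- k = 7, one model: 1 − 0.9^7 = 52.2%
- k = 7, two models: 1 − 0.9^14 = 77.1%

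**4. Simulation of the full procedure.** Settings: 100 patients; 20, 30 or 50 events; half binary and half continuous candidates; no true effects; screen at p < 0.10, then backward removal at 0.10; 2,000 replicates per setting. The entries are the chance of at least one variable in the final model, with ranges over the three event counts.

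| Candidates k | Formula, one model | Simulated, independent | Simulated, correlation 0.3 | Formula, two models |
|---|---|---|---|---|
| 3 | 27.1% | 26.3-27.5% | 26.0-26.7% | 46.9% |
| 7 (all named) | 52.2% | 50.2-52.4% | 46.2-50.6% | 77.1% |
| 10 (assumed) | 65.1% | 62.7-64.4% | 60.0-60.4% | 87.8% |
| 15 (assumed) | 79.4% | 78.2-80.5% | 72.1-72.8% | 95.8% |

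With correlation 0.3 and k = 7, two models give 1 − (1 − 0.462)² = 71% to 1 − (1 − 0.506)² = 76%. Together with the independent case, the range is 71-77%.

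**5. What drives the rate.**

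- It hardly changes between 20, 30 and 50 events. It changes strongly with k.
- In every setting the chance of a non-empty final model equalled the chance that at least one variable passed the screen. Backward elimination at the same threshold gave no protection against a false finding.
- With k = 7, at least one survivor also had p < 0.05 in 27-30% of analyses per model.

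**6. Direction of uncertainty.** Each candidate counts as one test. Testing tumour location or treatment by separate category terms would raise the figures.

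**The case against.** The strongest reply is that this is an exploratory observational study, that the regressions are not listed as outcome measures, and that an article abbreviates its variable lists. A closed list, and any validation, may stand in a document that is not shown. That is fair, so neither the open wording nor the absence of validation is a finding in itself. The selection rule is stated in full, however, and closing the list at the seven named variables would still give about 50% per model.

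The authors also make the analysis conditional on sufficient power. This shows caution, but power is a different quantity. The false-selection rate was nearly the same at every event count tried.

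The figures assume that no candidate has any effect. If some do, the study will find true predictors as well. The calculation describes what the procedure does with noise; it does not predict that this study's findings will be false.

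Some stronger readings are tempting, but the documents do not support them:

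- **Most single models would report a false predictor.** With the seven named candidates the chance is about even. A clear majority needs both models together or a longer list, which is an assumption.
- **The problem comes from the small sample.** It comes from 0.10 applied to each candidate.
- **The model would often exceed 3 covariates.** Under noise with k = 7, more than three variables passed the screen in under 1% of analyses. The mismatch lies in the number of candidates tried.
- **Discrimination would look good.** Apparent c-statistics of 0.64-0.67 under noise arise only where a predictor was retained (0.57-0.62 overall), and the article plans no such statistic.
- **The recurrence model supports only one or two covariates.** No recurrence count is given from which to derive this.

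**Conclusion.** The point holds. The plan combines a lenient univariable screen, unrestricted entry and backward removal at the same threshold, and then gives the survivors a label that the procedure cannot support. It does not apply the limit on which its own sample-size statement rests.

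Under complete noise, the seven named candidates give at least one false independent predictor in about half of analyses per model (46-52%) and about 71-77% over both models. With 10-15 candidates the rate is about 65-79% per model by the independence formula, and somewhat lower if candidates are correlated. These figures assume no true effects, one test per candidate, and independence between the two models.

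The consequence is over-optimistic odds ratios, p-values and intervals in the predictor analyses. The descriptive primary results (the share who withdraw and seizure freedom at 12 and 24 months) are not affected. A reader might infer that the protocol means the selected predictors to direct AED treatment. The Discussion says only that the results of the study as a whole may eventually guide recommendations.

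**What to change.** - **Decision model.** Replace the univariable screen and backward elimination with at most 3 degrees of freedom, named before any outcome analysis. Under noise, the chance of any p < 0.10 is then 1 − 0.9³ = 27%, and of any p < 0.05 it is 1 − 0.95³ = 14%. Alternatively, fit a closed, named list by penalised logistic regression.
- **Recurrence model.** Set the number of degrees of freedom from the observed number of recurrences before any predictor is examined, or use the same penalised approach.
- **Reporting.** Give univariable associations as description only, and do not call survivors at p < 0.10 significant independent predictors. If a prediction model is reported, add a bootstrap optimism correction that repeats every modelling step.

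The cost is a change of analysis wording and a short extra analysis. No further patients or data are needed. The downside is fewer predictors to report.

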#### Multivariable analysis

Next, a multivariable logistic regression analysis will be performed to identify independent predictors of the decision to withdraw AEDs. All variables that are univariately associated with this outcome measure will be entered as possible predictors in a multivariable logistic regression analysis. With a backward selection procedure, using a p-value of 0.10 as the removal criterion, significant independent predictors will be identified. Moreover, we will determine predictors of seizure recurrence. A similar analysis will be performed with seizure recurrence as dependent outcome variable. Variables (such as tumour location, pre-operative seizure frequency, response on MRI, etc.) will be entered as possible predictors in both multivariable logistic regression analyses, using the aforementioned criteria. Note that this analysis can only be performed in case of enough statistical power.

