In patients with non-tumour-related epilepsy AEDs are generally discontinued some time after successful epilepsy surgery [18],[27],[28]. AED withdrawal following temporal lobe resection in patients with refractory non-tumoural epilepsy eventually leads to seizure freedom without use of AEDs in 77% of patients [29]. In a review on AED management after epilepsy surgery, AED withdrawal was associated with a lower rate of seizure recurrence compared to AED continuation. Moreover, in 77% of patients whose seizures recurred after AED withdrawal, seizure freedom could be regained after restart of medication [30]. After surgery for paediatric epilepsy, seizure freedom was achieved in 77% of patients who completed AED withdrawal during follow-up. Early AED withdrawal did not affect long-term seizure outcome [31]. In general, epileptologists recommend to start tapering after at least one year of seizure freedom after epilepsy surgery, although the exact timing of AED withdrawal is controversial [32]-[35].

In patients with seizure freedom after anti-tumour therapy the question emerges whether AEDs should be continued, particularly in the case where anti-tumour treatment has been successful. In addition, several studies suggest that the efficacy of AEDs in brain tumour patients is limited. Up to 50% of brain tumour patients still have seizures despite AED treatment [13],[36].

Seizure frequency is likely to increase without AED treatment in glioma patients with ongoing seizures, warranting continued treatment. However, the necessity of AEDs in glioma patients with long-term seizure control is disputable. A few studies support the notion that seizure freedom in brain tumour patients can be maintained without AEDs. In one series 45 out of 62 (73%) children with a brain tumour whose AEDs were withdrawn after anti-tumour treatment became seizure free [37]. Small observational studies on AED use in meningioma and LGG patients showed ongoing seizure freedom after AED withdrawal in a majority of patients [38]. In case seizures reoccur, they are often associated with tumour recurrence [38]. Larger observational studies show that AEDs often are unable to prevent seizure recurrence in patients with renewed tumour growth [16].

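### The planned analysis guarantees no adjusted estimate of seizure recurrence after AED withdrawal versus continuation: a p-value filter decides whether the withdrawal term is reported

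*Protocol article*

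**What the plan says.** Under Design and overview, the protocol article names as an object of study "the effects of AED withdrawal or continuation on seizure freedom". Its second hypothesis predicts that withdrawn and continued patients will not differ significantly in seizure freedom at last follow-up. The Intervention section says that patient and physician choose together whether to withdraw, and then: "Two groups of patients will be analysed, depending on the outcome of the decision-making process". The second primary outcome is "seizure freedom at 12 months and 24 months of follow-up".

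The Statistical analyses section offers three things:

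- descriptive statistics;
- a univariate logistic screen at p < 0.10, run for the decision to withdraw and for seizure recurrence;
- a multivariable logistic model for each of these outcomes, with backward removal at 0.10.

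For the last of these, example variables (tumour location, seizure frequency before surgery, MRI response and others) "will be entered as possible predictors in both multivariable logistic regression analyses, using the aforementioned criteria". AED withdrawal is not named as a covariate in the recurrence model and is not kept in by rule. The section ends by making the analysis conditional on adequate power, without a threshold.

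**The concern.** A search for predictors and an estimate of an exposure effect are different tasks. For the second, the exposure has to be in the model whatever its p-value, and the adjustment variables should be fixed because they may drive both the decision and the outcome. Here the written rule treats withdrawal like any other candidate. Three outcomes are possible:

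- Withdrawal fails the screen or is removed. Only the crude contrast between self-selected groups is left.
- Withdrawal survives. It is then adjusted for whichever predictors also survived, but it is reported because the estimate came out large, so it is biased away from the null.
- The model is not run for lack of power. Again only the crude contrast is left.

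Because hypothesis 2 predicts no significant difference, a term dropped for non-significance is easily taken as confirmation. The Discussion expects to conclude that withdrawal does not substantially raise the risk of recurrence, so a comparative safety statement would rest on this.

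**Working it through.** **1. The plan's own figure.** The Sample size section says that 100 patients with at least 30 per group suffice for a model with 3 covariates. This reproduces as 30% × 100 = 30, and 30 / 10 = 3, if a rule of ten per variable was meant (my assumption; the article names no rule). For the recurrence model the count that matters is recurrences, not group size (step 4).

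**2. Inputs.** N = 100 and both p-value limits of 0.10 come from the article. The splits follow from its expectation that about half withdraw and its cautious estimate of 30%: 50/50 and 30/70 (withdrawn/continued). Recurrence rates by group are not given, so three assumed pairs are used. The screen is taken as two-sided.

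**3. How often withdrawal is lost.** For the first screen alone, with n = 50 per group:

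power = Φ[(|p₁ − p₂| − 1.645·SE₀) / SE₁], where SE₀ = √(2·p̄(1 − p̄)/n) and SE₁ = √([p₁(1 − p₁) + p₂(1 − p₂)]/n).

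- 10% vs 30%: SE₀ = 0.0800, SE₁ = 0.0775; (0.20 − 0.1316)/0.0775 = 0.88; power 0.81, so failure 0.19.
- 15% vs 27%: SE₀ = 0.0815, SE₁ = 0.0806; (0.12 − 0.1340)/0.0806 = −0.17; power 0.43, so failure 0.57.
- 20% vs 30%: SE₀ = 0.0866, SE₁ = 0.0860; (0.10 − 0.1424)/0.0860 = −0.49; power 0.31, so failure 0.69.

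Simulating the whole procedure (screen, then backward removal, with nine unrelated candidates beside withdrawal) gives, across the two splits:

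| Assumed recurrence, continued vs withdrawn | True OR | Withdrawal absent from final model |
|---|---|---|
| 10% vs 30% | 3.9 | about 21–25% |
| 15% vs 27% | 2.1 | about 60–61% |
| 20% vs 30% | 1.7 | about 70–74% |

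True OR = [p₁/(1 − p₁)]/[p₂/(1 − p₂)]; for example (0.27/0.73)/(0.15/0.85) = 2.1. In that middle case the median OR among studies that keep withdrawal is about 3.5. Repeat runs of the middle case gave up to 64% absent, which is simulation error.

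**4. Information available.** Expected recurrences in the middle case are 50 × 0.27 + 50 × 0.15 = 21, or 30 × 0.27 + 70 × 0.15 = 18.6. At ten per variable that supports about two terms. At 50/50 the standard error of the log OR is √(1/13.5 + 1/36.5 + 1/7.5 + 1/42.5) = 0.508, so even unadjusted the 95% interval is 2.10 × exp(±1.96 × 0.508), about 0.77 to 5.7.

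**5. Confounding of the crude contrast (illustration, all values assumed).** Suppose that 40% of patients carry a factor that raises recurrence from 10% to 30%, and that withdrawal has no effect.

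- Carriers withdraw less often (30% vs 63%). Withdrawn share: 0.4 × 0.30 + 0.6 × 0.63 = 0.498. Carriers among withdrawn: 0.12/0.498 = 24.1%; among continued: 0.28/0.502 = 55.8%. Crude recurrence is 10 + 20 × 0.241 = 14.8% vs 21.2%, so withdrawal looks about 6 points safer.
- Reverse the preference (carriers 63%, others 30%). Withdrawn share: 0.252 + 0.18 = 0.432. Carriers: 0.252/0.432 = 58.3% vs 0.148/0.568 = 26.1%. Crude recurrence is 21.7% vs 15.2%, so withdrawal looks about 6 points more harmful.

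The same mechanism can bias either way, and the article has no data that settle which.

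**The case against.** **The contrast is not the whole of the second primary outcome.** The primary outcome names no comparison. Design and overview also aims at the rate of successful withdrawals, the interim rule counts recurrences among withdrawers only, and the Discussion speaks of the risk once AEDs are withdrawn. Those are single-group risks, which descriptive statistics answer without adjustment. The Sample size section adds that group differences are not the study's main purpose. All this stands, and it lowers the weight of the point. It does not remove hypothesis 2 or the stated aim.

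**An adjusted analysis may well result.** A reader might infer that the plan contains none at all. The text does not support that: a multivariable recurrence model is planned, its variable lists are open-ended, and withdrawal, if entered and retained, would be adjusted for the other retained predictors. What is missing is a guarantee.

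**The direction of bias is not known.** A reader might take the Background review, in which "AED withdrawal was associated with a lower rate of seizure recurrence compared to AED continuation", as a sign that low-risk patients withdraw. That review concerns epilepsy surgery, and the article does not attribute its result to selection. Moreover, the recruitment procedure keeps patients whose physician foresees serious disadvantages of withdrawal out of both groups, which removes some confounding beforehand.

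**Detail left to a fuller document.** A named comparative model could sit in a full protocol or SAP. But the article itself fixes the selection rule, and following it gives the result above.

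**Conclusion.** The point holds in limited form and should be fixed before analysis. For hypothesis 2, the stated rules leave it to chance whether an adjusted estimate of the withdrawal contrast exists, and inflate it when it does. Depending on recurrence rates that the protocol does not give, withdrawal drops out in roughly a fifth to three quarters of studies. This rests on the assumed rates, nine unrelated candidates, and withdrawal being entered as a candidate at all. If it is not entered, the planned model gives no adjusted estimate of it. Confounding of the crude contrast is plausible, with unknown size and sign. The single-group rate of successful withdrawal and the interim rule are not affected.

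**What to change.** - For hypothesis 2, prespecify one recurrence model with the decided group (withdraw or continue) forced in whatever its p-value, and state its time point.
- Adjust for a very short list fixed in advance from the items under Baseline characteristics (for example date of last seizure, seizure history, histological subtype, past anti-tumour treatment), or for a single propensity-score term built from them. Either choice must stay within the three covariates of the Sample size section. With about 20 recurrences, group plus one score term is the safer count.
- Report the adjusted and the crude difference side by side, each with a 95% confidence interval, and do not make this analysis conditional on power.
- Keep the stepwise search as a separate, exploratory analysis, and the rate of successful withdrawal as descriptive.
- State that a non-significant result will not be read as showing no difference.

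The cost is a little more analysis on data already collected, with no extra patients or visits. Intervals will be wide: forcing the term in removes the selection bias but does not add information.
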